#### Assessment of safety endpoints

To assess the safety of the Pregnolia system the occurrence of any serious adverse event (SAE) during the study will be rated according to their seriousness and relatedness.

All SAEs that occur during the study period (from time of consent to delivery), whether considered to be related to the study medical device or not, must be reported via the case report form. Additionally, all adverse device effects shall be reported in the CRF.

Infections will be collected as an adverse event but displayed additionally to the planned general overview of adverse events (AE).

#### Other assessments

The cervical length and the uterocervical angle will be measured with the use of a transvaginal ultrasound: three (3) consecutive TVUS scannings of the uterine and cervical anatomy will be taken according to fetal medicine procedure [23]. The patients will be in a dorsal lithotomy position with the bladder essentially empty. The pressure from the ultrasound probe on the cervix should be as gentle as possible [24].

The cervix should be measured along its longitudinal axis. The UCA is the angle formed by the cervix and the lower uterine segment. The uterocervical angle (UCA) is measured on the image with the shortest cervix length (CL). First, a straight line is drawn between the external os and the internal os, including the isthmus. Second, a line parallel to the lower anterior uterine wall and passing through the end of the first line in the internal os is drawn (ideally 3 cm long). The angle given by the intersection of the two lines is measured and represents the UCA [25–27]. The ultrasound measurement of the UCA and CL is depicted in Fig 3.

**Fig 3 pone.0283944.g003:**
[figure not shown]
The measurement of UCA. From [25].

### Data management and confidentiality

The investigators will use CRFs with all relevant data of the participating subjects. CRFs will be kept monthly updated to reflect the patient’s status at each phase during the study. The data will be pseudonymized and only research study staff will have access to the identification key. The medical record might be reviewed on site by a monitor for source data verification or any other quality check or during an audit, however all involved staff is obliged to maintain confidentiality.

#### Data collection and follow-up for withdrawn participants

A patient can be withdrawn from the study participation at any time. In case a subject is withdrawn from the study, no further data for that subject will be collected, but the data already collected will be used for analysis. Since there is no risk for the subject, no further follow-up will be required.

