#### Criteria for withdrawal

The subjects will be advised in the Informed Consent Form that they have the right to withdraw from the study at any time without prejudice and may be withdrawn at the Investigator’s discretion at any time when this is considered to be in the interest of the subject. In the case that a subject drops out of the study or is withdrawn, the withdrawal / study termination page in a Case Report Form (CRF) shall be completed. On the withdrawal page of the CRF, the investigator should record the date of the withdrawal, the person who initiated withdrawal and the reason for the withdrawal. Reasonable effort should be made to contact any subject lost to follow up during the study in order to complete assessments and retrieve any outstanding data.

Withdrawal can be decided by the investigator due to an adverse event, a major protocol deviation that may lead to endangerment of the subject, a major protocol deviation concerning the primary outcome related to data quality, an investigator’s concern regarding subject’s health and withdrawal of informed consent. Discontinuation due to an Adverse Event should be documented in the CRFs.

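### The withdrawal rule ends all data collection even when the investigator withdraws the woman, so delivery data and SAEs obtainable from the medical record are lost needlessly and possibly selectively

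*Protocol article*

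**What the plan says.** All references are to the protocol article.

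- *Data collection and follow-up for withdrawn participants* sets one rule for every withdrawn woman: "In case a subject is withdrawn from the study, no further data for that subject will be collected". Data gathered before withdrawal are kept for analysis. The reason given for stopping is: "Since there is no risk for the subject, no further follow-up will be required".
- *Criteria for withdrawal* gives the investigator several grounds: "Withdrawal can be decided by the investigator due to an adverse event, a major protocol deviation that may lead to endangerment of the subject", then "a major protocol deviation concerning the primary outcome related to data quality, an investigator’s concern regarding subject’s health and withdrawal of informed consent". Revoked consent is one item on this list.
- The same section treats women who are lost to follow-up differently: "Reasonable effort should be made to contact any subject lost to follow up during the study in order to complete assessments".
- *Study endpoints* names delivery data as the secondary endpoint. *Study objectives* makes the correlation of initial CSI and CSI change with gestational age at birth the secondary objective.
- Table 2 and *Assessment of secondary endpoint* say that delivery data come from the medical record, post-partum, in the woman's absence.
- *Assessment of safety endpoints* requires reporting of "All SAEs that occur during the study period (from time of consent to delivery"), whether or not related to the device.

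**The concern.** Two different events are treated as one. When a woman revokes consent to the use of her data, collection should stop. When the investigator ends her study measurements, nothing prevents the already scheduled record review from supplying gestational age at birth, mode of delivery and complications. The rule discards these data in both cases.

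Three things are at stake:

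- **The secondary objective.** It loses outcomes that no later analysis can restore.
- **Possible bias.** Adverse events and health concerns in women with a short cervix are plausibly linked to early delivery. If so, the early births that carry much of the information on CSI and gestational age are the ones most likely to be missing.
- **Safety reporting.** Staff have incompatible instructions for a woman withdrawn before delivery: report SAEs until delivery, and collect nothing further. The no-risk rationale also sits badly beside a list of withdrawal grounds that includes adverse events and endangerment.

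**Working it through.** **1. The plan's own figure.** *Sample size calculation* gives 120 completers (60 per cohort), 15% dropout, and up to 142 enrolled (71 per cohort). Inflation by N/(1 − d):

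- 120/0.85 = 141.2, rounded up to 142
- 60/0.85 = 70.6, rounded up to 71

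Both figures reproduce.

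**2. Ceiling on the loss.** 71 − 60 = 11 women per cohort, and 11/71 = 15.5%. Over both cohorts this is 22 of 142. It is an upper limit under the planned dropout. The 15% also includes women lost to follow-up, whom the protocol pursues, and women who revoke consent, whose data the fix would not recover. The article does not divide dropout by reason.

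**3. Sections side by side for a woman withdrawn by the investigator before delivery.**

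| Item | Provision elsewhere | Withdrawal rule |
|---|---|---|
| Delivery data | Record review, woman absent | Not collected |
| SAEs up to delivery | Must be reported | Not collected |
| Baseline CSI | Primary endpoint | Kept |
| Follow-up CSI, if withdrawn before visit 2 | Primary endpoint | Lost, as it would be whenever measurement stops |

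Only the first two rows are avoidable losses.

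**4. Illustration: preterm birth rate in one cohort.** Assumptions, none from the documents: all 11 of 71 are withdrawn, the true rate is p, and withdrawn women have RR times the risk of retained women. With w = 11/71:

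- observed rate = p / (1 − w + w·RR)
- share of preterm births lost = w·RR / (1 − w + w·RR)

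| RR | True 10% | True 20% | True 30% | Preterm births lost |
|---|---|---|---|---|
| 1 | 10.0% | 20.0% | 30.0% | 15.5% |
| 2 | 8.7% | 17.3% | 26.0% | 22/82 = 26.8% |
| 3 | 7.6% | 15.3% | 22.9% | 33/93 = 35.5% |

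For p = 0.20: RR = 2 gives 0.20 × 71/82 = 0.173, and RR = 3 gives 0.20 × 71/93 = 0.153. At equal risk there is no bias, only lost events.

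**5. Bounds without a risk assumption.** Suppose 12 of 60 observed women deliver preterm (20%) and 11 outcomes are unknown. The rate among all 71 then lies between 12/71 = 16.9% and 23/71 = 32.4%.

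**6. Illustration on the stated objective, a correlation.** Bivariate normal CSI and gestational age were simulated with an assumed correlation of 0.30, and 15.5% of women were removed.

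| Removal depends on | Correlation among retained women |
|---|---|
| Nothing (random) | 0.30 |
| Early birth, moderately | 0.27 |
| Early birth, strongly | 0.25 |
| Low CSI and early birth together | 0.20 |

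Precision alone changes little. By Fisher's z, tanh(atanh r ± 1.96/√(n − 3)), the 95% interval at r = 0.30 is 0.128 to 0.455 with n = 120 and 0.142 to 0.443 with n = 142. The case for the fix therefore rests on possible selection and on the SAE conflict more than on numbers.

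**The case against.** The strongest reply is that little may be lost. The investigator's power to withdraw is optional. There are only two study visits, four weeks apart, and after them only record review remains. Early delivery is not a withdrawal ground, since women stay in the study until birth. *Risks / Benefits* reports no device-related serious adverse events so far. This is a pilot without formal power, its primary endpoint is CSI, and data collected before withdrawal are kept. All of this stands, and it limits the weight of the point. It does not supply a reason for discarding delivery data that are already due for abstraction.

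It can also be said that pursuing women lost to follow-up but not withdrawn women is coherent, because the former have not left the study. That is fair, and the difference is not a contradiction in itself. The SAE window might be read as closing at withdrawal, but the article's own parenthesis runs it to delivery, so the two sections need reconciling.

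Three stronger readings are tempting and are not supported:

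- *That a woman can be excluded for a bad CSI reading, which would make exclusion outcome-dependent.* The ground is "a major protocol deviation concerning the primary outcome related to data quality", which describes a deviation in procedure and not a CSI value. *Assessment of primary endpoint* has measurement failures recorded in the CRF and does not say that they lead to withdrawal. Such withdrawals may be unrelated to birth outcome and mainly cost numbers.
- *That birth outcomes are shown to be missing not at random.* No withdrawal rates by reason are given. Selection is an inference.
- *That the observed preterm rate could be roughly halved.* With a true rate of 20% and 70% among the 11 withdrawn, the observed rate is (71 × 0.20 − 11 × 0.70)/60 = 10.8%. This requires every dropout to be a withdrawal and 70/10.8 = 6.5 times the retained women's risk.

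**Conclusion.** The point holds on the text. The rule is unconditional, it reaches investigator-initiated withdrawal, nothing in the article exempts delivery data, and it conflicts with SAE reporting to delivery. Avoidable loss of secondary-endpoint and safety data follows directly for any woman so withdrawn.

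Selective loss is plausible for withdrawals due to adverse events or health concerns, but it is not documented. Its direction and size are assumptions. The ceiling is 11 of 71 outcomes per cohort, and the true number may be much smaller. At that ceiling, with two to three times the preterm risk in withdrawn women, a 20% rate would appear as about 17% to 15%.

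The harm falls mainly on a secondary objective of a pilot study. For the primary endpoint, baseline CSI is kept. This is a worthwhile and inexpensive correction, not a flaw that undermines the study.

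**What to change.** 1. In *Data collection and follow-up for withdrawn participants*, separate two cases. If study measurements stop for any reason other than withdrawal of consent to data use, continue to collect delivery data and SAEs from the medical record until the planned post-partum review, as far as the consent form allows. If the woman withdraws consent to data use, end collection at that point.
2. Reconcile the no-risk sentence with the adverse-event and endangerment grounds in *Criteria for withdrawal* and with the SAE window in *Assessment of safety endpoints*, so that staff have one instruction.
3. For a data-quality deviation, allow the affected CSI to be set aside while the woman's delivery data are still collected.
4. Record in the CRF which of the two cases applies. The withdrawal page already asks for date, initiator and reason.

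Cost: a small protocol amendment, which *Study approval and registration* would treat as formal if it changes study procedures, and possibly a check of the consent wording, because *Study population* ties use of record data to written consent. The consent form is not among the pages shown, so whether it already permits continued record review cannot be judged here. No visits are added, and the record review is already scheduled for every woman who stays in the study. Women withdrawn before visit 2 would contribute to the analysis of baseline CSI against gestational age, but not to the analysis of CSI change.

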#### Risks / Benefits

The study will be performed on pregnant women. While this study does not have direct impact on the pregnant women, the study results will help to provide better preterm birth management in the future. Pregnant women in emergency clinical settings will not be recruited.

Participants will undergo an additional procedure to quantify cervical stiffness. The study investigator will decide case by case if this additional procedure and the potential risk is acceptable for the pregnant women.

Each subject will undergo one speculum examination for checking the eligibility of the study, 3 consecutive TVUS cervical length and uterocervical angle assessments during two visits (it is an extra measurement only for the non-pessary cohort in the follow-up visit) and 3 consecutive cervical stiffness measurements during two visits.

Speculum examination and TVUS cervical length assessment are standard examinations for pregnant women and no additional risk is associated with this additional examination. The cervical stiffness measurement is done with the Pregnolia system. It has been CE-marked by TÜV Süd. Part of the registration process included a risk-benefit analysis of the Pregnolia system.

The Pregnolia System allows the assessment of cervical stiffness and its monitoring. The system provides an objective, more hygienic and less intrusive way of measuring cervical stiffness than cervical palpation. Possible side effects can be found in the Instruction for Use (IFU). However, the device seems to have a very good safety profile as the manufacturer received no serious adverse event reporting related to the medical device until now, neither in studies nor from the market.

The comparison of the benefits of the Pregnolia system with the risks shows that the benefit outweighs any of the potential risks considering their nature and frequency to prevent them.

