### Study objectives

The primary objective is to determine the absolute value of CSI and its change over time in women undergoing pessary treatment, in comparison to normal pregnancies, when measured at 18^+0^ to 24^+6^ weeks and at the follow-up visit (4 weeks later).

The secondary objective is to determine the correlation of the initial CSI and CSI changes with birth outcome (gestational age at birth).

The safety objective is the safety of the device, by assessing incidence, severity, and seriousness of device-related adverse events.

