### Study endpoints

The primary endpoint of the study is the Cervical Stiffness Index (CSI, in mbar). The secondary endpoint is patient delivery data (including gestational age, mode of delivery and complications). The safety endpoint is device-related adverse events (incidence, severity, and seriousness).

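### Withdrawal after a compromised baseline CSI keeps that reading in the analysis and gives up the 4-week CSI that could still be taken

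*Protocol article*

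**What the plan says.** Two sections of the protocol article have to be read together.

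- **Criteria for withdrawal** lists the grounds on which the investigator may withdraw a woman. The list opens "Withdrawal can be decided by the investigator due to an adverse event" and includes "a major protocol deviation concerning the primary outcome related to data quality". The primary outcome is the CSI (Study endpoints).
- **Data collection and follow-up for withdrawn participants** sets a single rule for all withdrawals: "no further data for that subject will be collected, but the data already collected will be used for analysis". It adds: "Since there is no risk for the subject, no further follow-up will be required".

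Three other places matter. Study objectives gives the primary objective as to "determine the absolute value of CSI and its change over time in women undergoing pessary treatment, in comparison to normal pregnancies", so both the level and the change are needed. Risks / Benefits states "3 consecutive cervical stiffness measurements during two visits", so there are only two occasions on which CSI is taken. Assessment of primary endpoint has a measurement failure noted in the CRF and attaches no rule for excluding the reading.

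**The concern.** The rule for withdrawn women does not depend on why they were withdrawn. For withdrawal of consent or a safety ground, stopping collection and keeping earlier data is an ordinary retention rule. For a data-quality ground it works badly when the compromised reading is the baseline one. The value that prompted the withdrawal is kept, and a 4-week measurement that might be sound is not taken.

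The reason given for ending follow-up is that the subject faces no risk. That concerns safety and does not explain why obtainable study data should be forgone.

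Both parts of the primary objective are touched. The doubtful value enters the baseline comparison, and the woman leaves the analysis of change. Her delivery data are also not collected, so she cannot contribute to the secondary objective on gestational age at birth. As written, the baseline CSI comparison is then the only CSI objective she informs, and it rests on the reading that was called into question.

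**Working it through.** **Inputs from the protocol article.** 60 women per cohort to complete, up to 71 recruited, 15% dropout (Sample size calculation). Two CSI visits with three readings each (Risks / Benefits; Table 2). The withdrawal ground and the data rule are as quoted above. No rate of data-quality withdrawal, no CSI standard deviation and no effect size is given.

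**Step 1, the plan's own figure.** Recruits = completers / (1 − dropout). Per cohort, 60 / 0.85 = 70.6, rounded up to 71. In total, 120 / 0.85 = 141.2, rounded up to 142. Both reproduce. The allowance is 71 − 60 = 11 women per cohort for losses of every kind.

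**Step 2, follow the two rules through time.**

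| Data-quality withdrawal occurs | CSI kept | CSI lost |
|---|---|---|
| at baseline, before any reading | none | baseline and 4-week |
| after a compromised baseline reading, before the 4-week visit | the compromised baseline | 4-week, and so the change |
| at the 4-week visit, before a reading | baseline, which may be sound | 4-week, and so the change |
| after a compromised 4-week reading | both, including the compromised one | none left to lose |

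Only the second row combines a retained doubtful reading with the loss of a later one. In the fourth row a doubtful reading is kept, but the further loss is limited to delivery data.

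**Step 3, size under an assumption.** Suppose k of the 71 women in a cohort fall in the second row and there is no other loss. Let e be the average error of their baseline CSI values as summarised for analysis. Then the shift of the cohort's baseline mean is (k / 71) × e, and the number with a CSI change is 71 − k.

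| k | Flawed share | Shift of baseline mean | Women with a CSI change |
|---|---|---|---|
| 1 | 1.4% | 0.014 × e | 70 |
| 3 | 4.2% | 0.042 × e | 68 |
| 5 | 7.0% | 0.070 × e | 66 |
| 11 | 15.5% | 0.155 × e | 60 |

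The last row would use up the whole dropout allowance and is an outer bound, not an expectation.

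To put this on a scale, assume further that e is 2 SD, always in the same direction. For k = 2, 4 and 6 the shift is (2/71) × 2 = 0.056 SD, (4/71) × 2 = 0.113 SD and (6/71) × 2 = 0.169 SD. If the errors average zero, there is no shift on average, only added noise. If both cohorts are affected alike, the shifts cancel in the comparison between cohorts.

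**The case against.** The best case for the plan has four parts.

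- **A poor reading is not in itself a withdrawal.** The ground requires a major protocol deviation, withdrawal is optional, and a failed measurement is simply noted in the CRF. This stands: it makes the event uncommon, but the rule is no better when the event occurs.
- **The harm is conditional.** A reader might infer that every data-quality withdrawal keeps bad data and discards good data, so that the rule defeats its own purpose. The documents do not support that. The measurement site is checked before the probe is applied, so withdrawal can precede any reading. After the 4-week visit no CSI remains to be lost. The protocol also states no purpose for this ground.
- **Analysis sets and validity rules belong in the analysis plan,** which is not shown, and the article is a condensed document. This stands in part. The retention sentence speaks of analysis in general and does not name the primary one, so an analysis plan could define which readings are valid. It would, however, have to narrow an unqualified sentence, and it could not supply a 4-week CSI that was never measured.
- **The size is assumed.** This also stands. There are three readings per visit and the way they are combined is left open, so one faulty reading may move a woman's summarised value by less than its own error. The study is a pilot without a formal power analysis, and its analysis is largely descriptive.

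A reader might also infer that an investigator could end a woman's follow-up because her CSI was unwelcome. Nothing in the article treats an unwelcome value as a protocol deviation, so this is conjecture.

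**Conclusion.** The point holds in conditional form. When a data-quality withdrawal follows a compromised baseline CSI and precedes the 4-week visit, the protocol as written keeps the doubtful reading and gives up the 4-week CSI, the CSI change and the delivery data. This is a consequence of two stated rules, not of missing detail.

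The effect is probably small. The documents give no rate, and every figure for the shift rests on an assumed number of women and an assumed error. Even the severe assumption of a 2 SD error in one direction gives about 0.06 to 0.17 SD for two to six women among 71. The 60 completers would be the wrong denominator for this, since a withdrawn woman is not a completer. The loss of each affected woman from the change analysis needs no assumption about error. The point is worth correcting because the correction is cheap and the lost measurement cannot be restored at analysis. The documents do not show that the primary comparison will be biased.

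**What to change.** In Criteria for withdrawal, make a data-quality deviation a reason to invalidate the affected CSI reading, not to withdraw the woman. State that the planned 4-week visit and the collection from medical records continue unless consent is withdrawn or a safety ground applies.

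In Data collection and follow-up for withdrawn participants, add that readings flagged invalid are excluded from the main CSI analysis, with a sensitivity analysis that includes them. The flag should follow technical criteria fixed in advance. It should be entered in the CRF at the time of measurement, and so before the birth outcome is known.

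The cost is a few words in two sections, one CRF flag and one extra analysis run. No separate blinded assessor is needed. Technical faults are seen by the operator at the bedside, and the CRF as described (three CSI values and any failure) would give a blinded assessor little to work from. Criteria fixed beforehand and recorded on the spot provide the main protection.
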